## Methods/Design

### Study design

This study uses a randomized controlled two-arm multiple follow-up design to: (1) test the effectiveness of the Decide2Quit intervention against usual smoking cessation care for hospitalized patients transitioning to outpatient care; and (2) determine the cost-effectiveness of each component of a smoking cessation intervention for hospitalized smokers (the Decide2Quit post-hospital intervention and usual care). The primary outcome for effectiveness is self-reported 30-day point prevalence at 6 month post-hospitalization. Secondary outcomes are: biologically confirmed smoking cessation at 6 months; 30-day point prevalence at 3 and 12 months; and 7-day point prevalence at 3, 6, and 12 months. Consecutive abstinence will be assessed using the three 30-day point prevalence data. The cost-effectiveness of the intervention compared to usual care will be determined by considering costs of intervention implementation and costs of healthcare with effectiveness measured in terms of Quality Adjusted Life Years (QALYs).

This study has obtained approval from The University of Alabama at Birmingham (UAB) Institutional Review Board for Human Use (IRB). All study personnel are IRB trained and Health Insurance Portability and Accountability Act (HIPAA) certified.

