### Data collection and measurements

Survey data collection takes place at the hospital bedside for baseline and via telephone interview for the 3- , 6- and 12-months follow-up. Additional biologic measures are collected at 6-month follow-up as described below. Tables 
2 and 
3 describe the measures to be collected at each time point. Measures are noted as Tier 1 (core across all collaborative projects), Tier 2 (optional measures, standard across projects), or Tier 3 (specific to this project). Study staff who conduct assessments are blinded to participant condition and are trained to collect all data uniformly according to written protocols. Data are entered directly into an internet-based survey system using security-enabled laptop computers with either WiFi (at bedside) or hard-wired internet access. All questions require responses by the system to facilitate complete datasets (‘refused’ and ‘does not know’ response options available). Study staff are trained to complete paper copies should there be difficulty in accessing the internet, with the study data manager later entering the data into the database. Some data are acquired from patients’ electronic medical records, study records, or outside sources, as noted in Table 
3.

**Table 2 T2:** General assessments and time-points

**Tier**^**a**^	**Measure**	**Details**	**Month**			
			**0**^**b**^	**3**	**6**	**12**
1	Demographics^c^	Age, length of stay, insurance, height, weight, ICD-9 codes, DRGs, Procedure codes, admission type, discharge ‘to’ plan, race, ethnicity, gender, education, marital status, other household smokers,	X			
1	Smoking status	Self-reported - last 7 days		X	X	X
1	Smoking status	Self-reported - last 30 days	X	X	X	X
3	Smoking status	Prolonged abstinence (multiple point prevalence)		X	X	X
1	Quit plan	Post-hospital plans regarding quitting	X			
1	Other tobacco use	Other than cigarettes-last 30 days	X	X	X	X
2	Tobacco dependence	Heavy Smoking Index (2 questions)	X	X	X	X
2	Tobacco cessation treatments	Behavioral and pharmacologic treatments, dose/frequency, length of use	X		X	X
3	Pack-history	Lifetime	X			
3	Longest abstinent period	Lifetime at 0 months; past year at 12 months	X			X
1/3	Satisfaction	Satisfaction with smoking cessation help		X		
3	Quit attempts	Past year (over 24 h abstinent)	X		X	X
3	Social support	Perceived support from significant others to quit/abstain	X		X	X
3	Internet and e-mail use	Frequency and type of use	X			

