### Data analyses

#### Primary and secondary outcomes analyses

The study analyses will be conducted using the most up-to-date version of SAS (SAS Institute, Cary, NC, USA) and *P* ≤ 0.05 will be considered significant for all analyses, except where Bonferroni correction for multiple comparisons is necessary. Baseline characteristics of both groups will be compared to ensure that random assignment results in comparable groups. Any factors not found balanced across randomization groups will be adjusted for in subsequent models. Continuous variables will be compared using a two-sample t-test, while a chi-square test of association will be used to compare categorical variables.

The primary outcome for this study will be self-reported 30-day tobacco abstinence rates at 6-months follow-up. For missing outcome data at the 6- and 12- months follow-ups, we will impute missing data using a propensity-based multiple imputation method 
[38] that has been agreed upon for the collaborative 
[39]. This approach assumes that non-response is random which is more robust than assuming all non-responders are smokers 
[40]. Using baseline and any additional available data (for example, 3-month survey), we will use a logistic regression model to estimate the propensity to respond to the follow-up survey for each hospital stratum and treatment arm combination. Within each combination we will stratify further based on values of the estimated propensities and then impute a value for the outcome for each non-respondent by randomly sampling from the respondent values within their sub-stratum. Multiple datasets will be created and the point estimates and the estimated standard error from each dataset will be combined to arrive at a single point estimate, its estimated standard error, and the associated confidence interval or significance test 
[40]. Given the potential for missing data not-at-random, we will further implement a pattern-mixture analyses 
[41] based on content experts and the observed patterns of missing data.

We will also run a responders-only analysis for descriptive purposes. A two-sample test for the difference in proportions will be used to test whether the quit rates are different between the two treatment conditions (two-sided) and, if indicated, whether the Decide2Quit intervention is effective in promoting smoking cessation compared to the usual care group (one-sided). We will conduct this same statistical analysis for secondary outcomes.

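### The stated imputation does not carry a patient's own earlier smoking status into the draw and names no rule for month 3, so consecutive abstinence built from it would be understated and its arm difference distorted

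*Protocol article*

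**What the plan says.** The Study design section of the protocol article lists consecutive abstinence with the secondary outcomes: "Consecutive abstinence will be assessed using the three 30-day point prevalence data". Table 2 schedules it at months 3, 6 and 12 as a measure specific to this site.

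The section on primary and secondary outcomes analyses gives the missing-data rule: "For missing outcome data at the 6- and 12- months follow-ups, we will impute missing data using a propensity-based multiple imputation method". The first step is a response model: "Using baseline and any additional available data (for example, 3-month survey), we will use a logistic regression model to estimate the propensity to respond". It is fitted within each combination of hospital stratum and treatment arm. Patients are then grouped by estimated propensity, and the plan will "impute a value for the outcome for each non-respondent by randomly sampling from the respondent values within their sub-stratum". Results from the multiple datasets are combined. A sensitivity analysis follows: "Given the potential for missing data not-at-random, we will further implement a pattern-mixture analyses". A responders-only analysis is planned for description. After the test of proportions, the section adds: "We will conduct this same statistical analysis for secondary outcomes".

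The article does not say whether consecutive abstinence is formed before or after imputation, or how a missing 3-month interview is treated.

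**The concern.** A response-propensity hot deck balances respondents and non-respondents on what predicts response. Under the assumption the plan states, that can be adequate for the abstinence rate at one visit. It does not aim to reproduce the association between visits within a patient. Someone abstinent at months 3 and 6 who misses month 12 receives roughly the sub-stratum's overall abstinence rate, not the much higher rate of patients who had already quit. A joint three-visit event depends on exactly that association.

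At stake is the trial's only sustained-cessation endpoint: its level in each arm and the comparison between arms. The 3-month outcomes also lack a clear rule, since imputation is named only for the two later interviews.

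**Working it through.** **Inputs from the article (Power estimate).** 744 per arm, 12% abstinent in the comparison arm, detectable difference 5.12 points (so 17.12% with intervention), 80% power, two-sided α 0.05.

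**Reproducing the plan's figure.** n = [1.960·√(2p̄(1−p̄)) + 0.842·√(p₁(1−p₁) + p₂(1−p₂))]² / (p₂−p₁)², with p₁ = 0.12, p₂ = 0.1712, p̄ = 0.1456. This gives 743.8, so 744 per arm. The stated figure is confirmed, and 12% and 17.12% are used below.

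**Assumptions not in the article.** The same abstinence rate p at every visit; 75% of month-3 quitters abstinent at month 6; 80% of month-6 quitters abstinent at month 12; month-12 status depends on month 3 only through month 6. Month 3 is complete. A fraction m is missing independently at months 6 and 12, and response is unrelated to earlier status.

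**True rate.** p × 0.75 × 0.80 = 0.60p: 7.20% and 10.27%, difference 3.07 points.

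**Rate after separate visit-wise draws.** A missing value is abstinent with probability p whatever the patient's history. Let s be the chance that a month-3 quitter is abstinent at month 12: s = 0.60 + 0.25q, where q = 0.20p/(1−p) keeps the month-12 rate at p. For p = 0.12, q = 0.0273 and s = 0.607. For p = 0.1712, q = 0.0413 and s = 0.610. Then

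R = p·[(1−m)²·0.60 + m(1−m)·0.75p + m(1−m)·p·s + m²p²].

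At m = 0.20:
- Comparison: 0.12 × (0.3840 + 0.0144 + 0.0117 + 0.0006) = 4.93%, or 0.68 of the truth.
- Intervention: 0.1712 × (0.3840 + 0.0205 + 0.0167 + 0.0012) = 7.23%, or 0.70 of the truth.
- Difference: 2.30 points against 3.07.

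| Missing, comparison / intervention | Comparison | Intervention | Difference (truth 3.07) |
|---|---|---|---|
| 10% / 10% | 6.01% | 8.68% | 2.67 |
| 20% / 20% | 4.93% | 7.23% | 2.30 |
| 30% / 30% | 3.95% | 5.92% | 1.96 |
| 30% / 15% | 3.95% | 7.94% | 3.99 |
| 40% / 10% | 3.09% | 8.68% | 5.60 |
| 15% / 30% | 5.45% | 5.92% | 0.46 |

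A simulation with 400,000 patients per arm, drawing within response-propensity quintiles, agrees to within sampling error: differences of 2.67, 2.39 and 2.05 for the equal cases, and 3.81, 5.55 and 0.55 for the unequal ones.

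**When earlier status predicts response (simulation, 20% missing, restricted to month-3 responders).** If month-3 quitters are more likely to respond with a log-odds of 1, the estimates are 6.3% and 9.1% (difference 2.8). At a log-odds of 4 they are 7.1% and 10.3%, and the bias nearly vanishes. If quitters are less likely to respond (log-odds −1), the comparison rate falls to 4.0%, worse than with no association.

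**Month 3.** If a missing month 3 is counted as smoking, the simulated differences at 10%, 20% and 30% missing per interview fall to 2.4, 1.9 and 1.4. Restricting to month-3 responders adds no bias when month 3 is missing completely at random.

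**Primary outcome.** At 20% missing in both arms and response unrelated to earlier status, the imputed 6-month rates were 12.0% and 17.2%, so the single-visit comparison is intact.

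**Joint alternative.** Modelling the three visits together from each patient's observed statuses returned about 7.2% and 10.3%, difference about 3.1, in every scenario, including unequal missingness.

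**The case against.** The strongest case against has five parts.

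1. **Order of operations.** The article does not say that visits are imputed separately and then combined. If the consecutive indicator is itself the imputed outcome, this mechanism need not apply. That stands, and the point is conditional on it. It is not a safe escape, though. Suppose an observed smoking report settles the outcome as failure and only undetermined patients are drawn from the respondents' composite rate. At 20% missing the comparison arm then gives 0.64 × 7.2% + 3.09% × 0.072 = 4.8%, where 3.09% is the share with no observed smoking and at least one gap. Redrawing every incomplete patient avoids that shortfall when data are missing completely at random, but it can turn a patient who reported smoking into a sustained quitter.

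2. **Earlier data enter the propensity model.** True, and the loss falls when earlier quitters are clearly more likely to respond. A moderate association leaves 6.3% against 7.2%.

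3. **Other analyses.** The pattern-mixture analysis addresses data missing not at random, whereas this bias arises even when data are missing at random. The responders-only analysis keeps the within-person link but is descriptive.

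4. **An article leaves detail to the full plan.** That covers the derivation of the composite. It does not cover a method that is stated concretely and does not suit this endpoint.

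5. **Limited reach.** The endpoint is secondary and site-specific. That stands.

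Two stronger readings are tempting. A reader might infer that the arm difference is always biased towards zero; the unequal-missingness rows show it can also be inflated. A reader might also infer that the 3-month outcomes will be analysed in responders only. The article does not say so, and its statement that secondary outcomes get the same analysis can be read as extending the imputation to month 3 or as covering only the test of proportions.

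**Conclusion.** The concern holds conditionally. If months 6 and 12 are imputed as described and then combined with month 3, the sustained-quit rate is understated. With equal missingness of 10%, 20% and 30%, the comparison-arm estimate is about 0.83, 0.68 and 0.55 of the truth. The arm difference is distorted: shrunk when missingness is similar across arms, and inflated or shrunk further when it differs. These sizes rest on assumed persistence, assumed missingness and a response propensity unrelated to earlier status; none of these figures is in the article. The article does not settle how month 3 is handled or whether the composite is formed before or after imputation. The 6-month primary outcome is not harmed by this mechanism when missingness is similar across arms. The matter should be settled before analysis, but it does not threaten the trial's main conclusion.

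**What to change.** For consecutive abstinence and the 3-month outcomes, impute status at months 3, 6 and 12 jointly or in sequence, separately by arm. Each visit's model should condition directly on the patient's observed or imputed status at the other interviews, for example by chained logistic models or by donors matched on smoking status at those interviews. Derive consecutive abstinence within each completed dataset, then combine across datasets. State explicitly how a missing 3-month interview is handled.

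The collaborative's agreed method can stay for the 6-month primary outcome. The cost is revised analysis wording, a little extra programming and a second imputation model to document; no data collection changes.

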### Participant recruitment and randomization to condition

Study staff verify eligibility with a screening assessment that includes questions about internet access and use of e-mail, the participation of other household members in this study, and mental status (if in question). Eligible patients are provided an overview of the study and a chance to ask questions prior to providing written informed consent. After completion of baseline assessments and listing on the electronic study roll by study staff, patients are randomized to study condition (intervention or usual care). Blocked randomization within each PCA is used to reduce selection and accidental bias and achieve balance in the allocation of participants to treatment arms. The study statistician generated random number lists for each PCA prior to study initiation. The Study Coordinator identifies the participants to randomize to study condition each day based on their order of listing on the study roll and the allocation indicated for the PCA in which they were recruited. As participants are allocated to the intervention arm, the Study Coordinator sends email alerts to designated hospital staff (Quit Staff) that newly randomized patients need to be registered to the intervention website, Decide2Quit. Figure 
1 depicts the recruitment and initial study activities flow.

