### Power estimate

Power is estimated for the primary outcome: differences in self-reported smoking abstinence rates between the two treatment conditions at 6 months post-hospitalization based on 30-day point prevalence. Rates for smoking cessation reported in the literature for ‘usual’ post-hospitalization care are 5% to 15% at 6 months and 7% to 10% at 1 year 
[37]. With 1,488 participants, 744 assigned to each treatment condition, using 12% as an estimated rate for the comparison group, this study will be powered (β = 80%-type II error, α = 0.05-type I error) to detect a difference of 5.12% between the two treatment conditions (two-sided). For the intervention condition, a sub-analysis between the group with one of three diagnoses (CHF, AMI, or pneumonia-expected *n* = 256) and the group with all other diagnoses (expected n = 488) will have sufficient power (β = 80%-type II error, α = 0.05-type I error) to detect a difference in tobacco abstinence rates of 9.4% (two-sided), assuming the three-diagnoses comparison group has a 25% quit rate (two-sided). Note that, as the smoking cessation rate increases for the comparison group, a larger difference is necessary between groups to achieve a specific level of power, which is why a higher rate is used for power computation. The reverse of this is true as well: as the comparison group rate decreases, a smaller difference between groups achieves the same level of power.

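### The printed imputation of the primary outcome draws donors without carrying their uncertainty, so the pooled standard error is somewhat too small; the undefined hospital stratum could make this worse

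*Protocol article*

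**What the plan says.** In the Protocol article, under Primary and secondary outcomes analyses, missing 6- and 12-month outcomes are to be filled in by a propensity-based multiple imputation agreed for the collaborative. The steps are printed in order:

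- Baseline and any other available data, such as the 3-month survey, enter a logistic model to "estimate the propensity to respond to the follow-up survey for each hospital stratum and treatment arm combination".
- Each combination is divided further by estimated propensity.
- The outcome step is to "impute a value for the outcome for each non-respondent by randomly sampling from the respondent values within their sub-stratum".
- Several datasets are made, and their estimates and standard errors are combined into one estimate, interval and test.

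The test is judged at the usual level ("0.05 will be considered significant for all analyses, except where Bonferroni correction"), and the same analysis is applied to the secondary outcomes. A pattern-mixture analysis and a descriptive responders-only analysis are also planned.

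The article does not say what a hospital stratum is. The trial runs in one hospital, in 27 of its PCAs (Setting and sample). The section Participant recruitment and randomization to condition names the only stratification that the article spells out: "Blocked randomization within each PCA is used to reduce selection and accidental bias".

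**The concern.** Two features of the printed rule matter.

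The first is the draw. For pooled standard errors to be right, the imputations must vary as much as our ignorance of the missing values does. That ignorance includes not knowing the true quit rate among donors. Sampling straight from the observed respondents fixes that rate at its sample value in every dataset. The between-imputation variance is then too small, and so is the pooled standard error. The error runs in one direction, towards false positives, and it falls on the primary test.

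The second is the size of the cells. If the stratum is the PCA, both the response model and the donor pools rest on very few patients, and the shortfall grows.

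**Working it through.** **Inputs from the article.** "With 1,488 participants, 744 assigned to each treatment condition, using 12% as an estimated rate for the comparison group" (Power estimate); two-sided alpha 0.05; 27 PCAs. **Assumed, because not stated:** 10% to 40% missing at 6 months, 10 imputations and, where used, five propensity classes.

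**1. The plan's own figure.** For 12% against 17.12%, with pooled variance under the null and no continuity correction:

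n = [1.960·√(2 × 0.1456 × 0.8544) + 0.8416·√(0.12 × 0.88 + 0.1712 × 0.8288)]² / 0.0512² = 744 per arm.

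The power is 80.0%. The stated detectable difference of 5.12 points is reproduced and is not in dispute.

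**2. The plain draw, whatever the strata.** Take one arm of n patients, a fraction f missing, outcome variance s², and M imputations.

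- Within-imputation variance: W = s²/n.
- Between-imputation variance with plain donors: B = f·s²/n.
- Reported variance: T = W + (1 + 1/M)·B.
- True variance: V = s²/[n(1 − f)] + B/M.

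At f = 0.2 and M = 10, T = 1.22·s²/n and V = (1.25 + 0.02)·s²/n. The SE ratio is √(1.22/1.27) = 0.980, and type I error is 2·[1 − Φ(1.96 × 0.980)] = 5.5%.

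| Missing | 10% | 20% | 30% | 40% |
|---|---|---|---|---|
| Reported SE / true SE | 0.995 | 0.980 | 0.955 | 0.919 |
| Type I error | 5.1% | 5.5% | 6.1% | 7.2% |

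The number of imputations hardly matters. From M = 5 to very large M, the 30% column stays at 6.1% to 6.15% and the 40% column at 7.1% to 7.2%.

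**3. Cell sizes if the stratum is the PCA.**

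- 27 × 2 = 54 cells, and 1,488/54 = 27.6 patients per cell.
- At 10% to 40% missing, each logistic response model has 2.8 to 11.0 non-respondents.
- With five classes there are 270 cells of 1,488/270 = 5.5 patients. These hold 5.0 down to 3.3 donors, and 0.6 down to 0.4 expected quitters at a 12% rate.

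**4. Simulation under no effect.** Settings: N = 1,488, 12% quit rate, 10 imputations, 4,000 replicates (Monte Carlo SE about 0.3 to 0.5 points), PCAs of equal expected size and known propensity classes. A cell without a donor borrowed from its PCA and arm. Entries are type I error.

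| Cells and draw | 10% | 20% | 30% | 40% |
|---|---|---|---|---|
| Arm × 5 classes, plain | 5.1% | 5.0% | 6.5% | 7.3% |
| Arm × 5 classes, bootstrap | 4.5% | 5.5% | 5.3% | 5.2% |
| PCA × arm, plain | 5.5% | 6.0% | 6.0% | 7.5% |
| PCA × arm, bootstrap | 5.0% | 5.2% | 4.7% | 6.0% |
| PCA × arm × 5, plain | 5.6% | 7.2% | 8.2% | 12.0% |
| PCA × arm × 5, bootstrap | 5.5% | 6.7% | 7.5% | 9.7% |

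In the 270-cell case with plain donors, the SE ratios are 0.97, 0.93, 0.88 and 0.81. A further set of 8,000 replicates for that case gave 5.6%, 6.9% and 8.9% at 10%, 20% and 30% missing.

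In the coarse cells the draw alone causes the excess, and resampling the donor pool largely removes it. In 270 cells sparseness is the larger cause, and resampling alone does not repair it.

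**The case against.** The strongest reply is that PCA cells are not in the text. The article says PCA where it means PCA, and it does not do so here. The method was agreed across several CHART sites, so the stratum may simply be the hospital. With one hospital there would be two first-level cells of 744. Five classes would then hold about 149 patients each, with about 119 donors at 20% missing, and the sparseness argument would vanish. The excess left at 10% to 20% missing would be about 5.0% to 5.5% in most runs, with one repeat near 6.0% at 20%, which is hard to tell from 5% by simulation. The number of classes also matters: under the PCA reading with two classes, type I error was about 5.3%, 6.2% and 6.7% at 10%, 20% and 30% missing. Finally, the article condenses a fuller plan and cites sources for the method, so a resampling step may be specified there.

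Much of this stands. A reader might infer that the plan fixes 54 or 270 cells and that the primary test therefore runs at 7% to 9%. The documents do not support that, because the stratum, the number of classes, the number of imputations and the missing rate are all unstated. Nor do donor pools without a quitter show bias: when values are missing at random within cells, the draws stay unbiased and only the variance suffers.

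The reply does not remove the point about the draw. The article sets out the algorithm step by step, and the outcome step as printed is a plain draw. The pattern-mixture and responders-only analyses do not correct the standard error of the primary test.

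**Conclusion.** The point holds in a limited form. As printed, the imputation is not proper, and the pooled standard error for the primary outcome is too small on any reading of the strata. The effect is negligible at 10% missing, slight at 20%, and worth correcting at 30% to 40%.

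The larger figures, about 7% at 20% missing and 8% to 9% at 30%, apply only if the stratum is the PCA and about five propensity classes are used. At 10% missing even that case gives 5.6%, within about two Monte Carlo standard errors of 5%. The PCA is a natural reading in a one-hospital trial randomized by PCA, but it is not a stated one. The article should settle it, because under that reading the separate response models are too sparse to be useful.

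**What to change.** Before the 6-month outcomes are analysed by arm:

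1. Define the hospital stratum.
2. Fit one response-propensity model per arm, with PCA (small PCAs pooled) and 3-month status among the covariates.
3. Form about five propensity classes within each arm.
4. Draw donors by an approximate Bayesian bootstrap: for each dataset, resample the class's donor pool with replacement, then impute from the resampled pool.

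Steps 2 to 4 belong together, since resampling alone does not rescue very small cells. Arm-level classes with resampled donors gave type I error of 4.5% to 5.5% and SE ratios of 0.98 to 1.01 over 10% to 40% missing.

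The collaborative's propensity approach is kept and no new data are needed. The cost is revised wording, a small code change, and confidence intervals wider by roughly the shortfall shown above.

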Several covariates may affect the relationship between the intervention effect and the quit rate. Potential covariates include age, tobacco dependence, major health issue, number of diagnostic codes assigned at hospital discharge, race, smoking history, alcohol use, depressive symptoms, social support, use of other smoking cessation programs, and self-efficacy. Because participants are randomized to treatment arm, these potential covariates will theoretically be balanced across the two arms. However, the strength of the association between each of these covariates and the quit rate will be assessed in a logistic regression model. This analysis will provide the variables that are predictive of smoking cessation among all smokers and can be repeated to test for predictors among the three diagnostic groups (AMI, pneumonia, and CHF) *vs* all other diagnostic groups. Secondary exploratory analyses are planned to investigate a range of broader issues related to smoking cessation. An analysis similar to the primary analysis will test potential differential effects of the Decide2Quit intervention among diagnostic groups by comparing those patients with AMI, CHF, and/or pneumonia to patients not having these diagnoses. A third set of tests of proportions will compare each of the three diagnostic groups of interest in the intervention condition to their matching group in the usual care condition (although power will be limited due to small sample sizes). The relationship between dose and smoking cessation will be examined using logistic regression tests, as we expect dose will not be normally distributed.

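### The named primary test leaves out the PCA randomisation strata and prespecified baseline covariates, giving up modest precision, and the conditional one-sided test should go

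*Protocol article*

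**What the plan says.** All references are to the protocol article.

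- **Randomisation** (Participant recruitment and randomization to condition): "Blocked randomization within each PCA is used to reduce selection and accidental bias". The Setting and sample section puts the number of participating PCAs at 27. Allocation follows completion of the baseline assessments.
- **Primary comparison** (Primary and secondary outcomes analyses): "A two-sample test for the difference in proportions will be used to test whether the quit rates are different between the two treatment conditions", two-sided. PCA and covariates do not appear in it.
- **One-sided test** (same section): if indicated, a further test asks "whether the Decide2Quit intervention is effective in promoting smoking cessation compared to the usual care group (one-sided"). No trigger and no separate significance level are given, and P ≤ 0.05 is the general threshold. The same procedure is extended to the secondary outcomes.
- **Adjustment** (same section): baseline characteristics are compared between arms by t-test or chi-square test, and any factor found unbalanced is to be adjusted for in later models.
- **Covariates** (same section): after a list of potential covariates, "the strength of the association between each of these covariates and the quit rate will be assessed in a logistic regression model". The stated purpose is to identify predictors of quitting.
- **Imputation** (same section): response propensity is modelled from baseline and other available data, within each combination of hospital stratum and arm.
- **Power** (Power estimate): "With 1,488 participants, 744 assigned to each treatment condition, using 12% as an estimated rate for the comparison group", the detectable two-sided difference is 5.12 points at 80% power.

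**The concern.** When allocation is balanced within strata, a test that ignores the strata uses a standard error that is too large to the extent that outcome differs between strata. Omitting covariates that predict quitting also leaves explainable variation in the error term. Tables 2 and 3 schedule the relevant data at month 0 (dependence index, self-efficacy, quit plan and others), so this precision could be had without new data or patients.

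The adjustment rule that does exist is a weak one. In a randomised trial, baseline imbalance arises by chance, and a covariate matters for precision because it predicts outcome, not because it happens to be unbalanced. The rule lets the observed data decide whether the treatment comparison is adjusted and for what. It also sits awkwardly beside the named test, which has no place for a covariate.

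The one-sided test adds a second route to a superiority claim, and its condition is not defined.

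**Working it through.** **1. The plan's own figure.** Inputs from Power estimate: n = 744 per arm, p0 = 0.12, p1 = 0.12 + 0.0512 = 0.1712, two-sided α = 0.05, power 80%.

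n = [z(α/2)·√(2·p̄·q̄) + z(β)·√(p0·q0 + p1·q1)]² / d²

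- p̄ = 0.1456, so √(2 × 0.1456 × 0.8544) = 0.4988, and × 1.960 = 0.9776
- √(0.1056 + 0.1419) = 0.4975, and × 0.8416 = 0.4187
- n = (0.9776 + 0.4187)² / 0.0512² = 744 per arm, power 80.0%

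The figure reproduces for the unadjusted two-sided test without continuity correction. The continuity-corrected version needs 783 per arm and the one-sided version 586, so neither was used.

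**2. Omitting PCA: test size.** The article gives no between-PCA variation, so SDs of 3, 5 and 8 percentage points in quit rate are assumed. The share of outcome variance between PCAs is s = SD² / (0.1456 × 0.8544), that is 0.7%, 2.0% and 5.1%. Approximate size of the nominal 5% test is 2·[1 − Φ(1.96/√(1 − s))]:

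| SD (points) | s | Size |
|---|---|---|
| 3 | 0.7% | 4.9% |
| 5 | 2.0% | 4.8% |
| 8 | 5.1% | 4.4% |

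**3. Omitting PCA and covariates: simulation.** 2,500 trials per cell, 27 PCAs, permuted blocks of 4 (assumed), PCA effects and one baseline prognostic score on the logit scale with assumed SDs. The comparators were a Cochran-Mantel-Haenszel test by PCA and a linear model with PCA plus the score and robust standard errors.

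| PCA SD / score SD | Unadjusted | PCA only | PCA + score |
|---|---|---|---|
| 0.3 / none | 80.2% | 80.5% | n/a |
| 0.6 / none | 81.7% | 82.6% | n/a |
| 0.3 / 0.7 | 80.2% | 80.5% | 82.9% |
| 0.6 / 1.0 | 80.2% | 81.1% | 84.4% |

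Under no effect, the unadjusted test rejected in 4.3% to 5.2% of trials. Simulation error on a single power figure is about √(0.8 × 0.2 / 2500) = 0.8 points, so the PCA-only gains are best read as 0 to 1 point.

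**4. Omitting covariates: effective sample size.** If baseline covariates explain a share R² of outcome variance (assumed), the adjusted analysis behaves roughly like n = 744/(1 − R²) per arm:

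| R² | Effective n per arm | Power | n per arm for 80% |
|---|---|---|---|
| 0 | 744 | 80.0% | 744 |
| 0.01 | 752 | 80.4% | 737 |
| 0.02 | 759 | 80.8% | 730 |
| 0.05 | 783 | 82.0% | 707 |
| 0.10 | 827 | 84.0% | 670 |

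For R² of 0.01 to 0.10 the gain is therefore 0.4 to 4 points.

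**5. The one-sided test.**

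- Run only after a significant two-sided result: total error stays at 0.05, of which 0.025 is in the direction of benefit. The test adds nothing.
- Run at 0.05 after a non-significant two-sided result: error is 0.025 (harm) + 0.05 (benefit) = 0.075. The chance of a false superiority claim is 0.05 instead of 0.025, and nominal power rises from 80.0% to 87.7%. The observed difference needed falls from 1.960 × 0.4988/√744 = 3.6 points to 1.645 × 0.4988/√744 = 3.0 points.

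**The case against.** The strongest reply is that nothing in the primary test is wrong. It is the test the trial was powered for, and leaving out the strata makes it conservative if anything. A reader might infer that it is invalid or that the 80% power fails; sections 1 to 3 of the working show neither. This part of the reply stands.

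A reader might also infer that stratum and baseline data are ignored. They are not: both enter the imputation, and an imbalance-triggered adjustment is planned. What remains is that neither puts a prespecified stratum or covariate term into the treatment comparison.

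The size of the covariate gain is fairly challenged too. The article calls these variables potential covariates and leaves their strength to be assessed, so they cannot be called strong predictors, and at an R² of 0.01 to 0.02 the gain is under 1 point. Nor can the case be enlarged by assuming a dropout rate, because the article states none and plans multiple imputation.

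On the one-sided test, a reader might infer that it can only loosen the error rate. The wording does not support that. The two-sided test comes first, and the natural reading is a directional follow-up to a significant result, which leaves error unchanged. The fallback reading is possible only because the condition is undefined. A full analysis plan might define it, but on either reading the test does no useful work.

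**Conclusion.** The point holds as one of efficiency and clear specification, not of validity. The article fixes an unadjusted primary test for a trial randomised within PCAs. Its one adjustment rule for the treatment comparison is data-driven and does not fit that test.

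The cost is about 0 to 1 point of power for PCA and about 0.4 to 4 points for covariates. These figures rest on assumed between-PCA variation, block size and R² (0.01 to 0.10). They are also approximations: the simulation used a linear model, not the standardised logistic model recommended here.

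The one-sided test is redundant on the natural reading. Total error reaches 0.075 only if it serves as a fallback at 0.05. The change is worth making because it is nearly free, not because the trial would otherwise fail.

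**What to change.** - Make the primary analysis a two-sided risk difference, standardised from a logistic model containing arm, PCA (sparse PCAs grouped by a prespecified rule) and a short fixed list of covariates measured at month 0 before randomisation, for example dependence index, self-efficacy and quit plan.
- Exclude discharge-coded diagnoses, the count of discharge codes and later use of cessation programmes. The notes to Table 2 say some record-based data are collected after discharge, so these may be recorded after randomisation.
- Fit the model within each imputed dataset and combine the results as already planned.
- Let this model replace the imbalance-triggered rule, and keep the unadjusted two-sample test as a sensitivity analysis.
- Delete the conditional one-sided test for the primary and secondary outcomes.

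The cost is revised analysis wording and minor programming. No new data or patients are needed, and standardisation keeps the risk difference as the quantity estimated.
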